**Methods/design:**

The PMP will be offered to federally qualified health centers and charity clinics in the Greater Houston area using a non-randomized stepped wedge design. Due to practical constraints of implementing and adopting in the real-world, randomization of start times and blinding will not be used. Any potential confounding or bias will be controlled in the analysis. Outcomes such as appointment adherence, patient referral to diagnostics, time to diagnostic referral, patient referral to treatment, time to treatment referral, and budget impact of the intervention will be assessed. Assessment of constructs from the consolidated framework for implementation research (CFIR) will be assessed during implementation and at the end of the study (sustainment) from each participating clinic. Data will be analyzed using descriptive statistics (chi-square tests) and generalized estimating equations (GEE).

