### Sample size

Sample size for the stepped wedge design is calculated using the formula of Woertman et al. 2013 [32], which corrects a standard sample size calculation for two independent proportions as follows:$$ Nsw= Nu* DEsw $$

where *Nu* equals the uncorrected sample size estimate and *DEsw* is the design effect for the stepped wedge design.$$ DEsw=1+\rho \left(ktn+bn-1\right)*\frac{3\left(1-p\right)}{\left(1+p\right)\left(\frac{1}{2ktn}+bn-1\right)2t\left(k-\frac{1}{k}\right)} $$

where *ρ* equals the intraclass correlation, *k* equals the number of steps, *b* equals the number of baseline measurements, *t* equals the number of intervention measurements, and *n* equals cluster size. The uncorrected sample size for a difference in two independent proportions assuming a baseline no-show rate of 35 % reduced to 28 %, an α of 0.05 and a power of 0.9 equals 924 per group. The average no-show rate and expected reduction in no-shows are based on pilot studies [20, 30]. The intraclass correlation coefficient (ICC), *p*, for mammography screening interventions has been shown to range from 0.0009 to 0.22 in community-based trials with an average ICC of 0.06 based on recent systematic reviews [33, 34]. Estimated sample sizes based on these parameters are summarized in Table 1. Based on the average reported ICC, the required sample size is 388 women. The required number of clusters is calculated as *Nsw/n* resulting in an effective sample size requirement of seven clusters (clinics) [32]. In order to account for potential attrition estimated based on the investigator’s pilot study, the sample size will be increased by 20 % to 466 women across nine clinics.

**Table 1 Tab1:** Estimated sample sizes based on ICC reported values

*Nsw*	*Nu*	*DEsw*	*p* (ICC)
370	1848	0.20	0.006
388	1848	0.21	0.06
370	1848	0.20	0.1
333	1848	0.18	0.22

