### Blinding

Due to the nature of the intervention, it is not possible to blind the clinics or the research team in this study. However, outcome assessment is objective as we are using medical records to obtain screening outcomes. It is also not possible to blind the data analyst because the analysis is designed as a time series in which every clinic receives the intervention rather than a comparison between groups. The analysis will be pre-specified rather than blinded, and any analysis not pre-specified will be clearly delineated and considered hypothesis generating/exploratory rather than hypothesis testing/explanatory.

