### Statistical methods

Descriptive statistics will be calculated for all primary and secondary measures. Following descriptive analysis, regression modeling will be used to evaluate outcomes while allowing for control of potential confounders (e.g., time, clinic size, staffing, and whether or not the clinic had a pre-existing patient navigation program for breast cancer screening). Due to the correlated nature of the data and repeated observations taken on each clinic, generalized estimating equations (GEE) will be used to model outcomes while allowing us to control for potential confounders [38, 39]. GEE is used to estimate the parameters from a generalized linear model when there is possible correlation between outcomes [38, 39]. GEE is a population averaged model that estimates the average response from a change in a covariate over the population rather than individual [38, 39]. GEE model estimates are less sensitive than generalized linear mixed models to the specification of the variance structure in the data making them a flexible choice [38, 39]. Data on appointment adherence will be analyzed using various sub-groups to evaluate the intervention effect. For example, no-shows and not attended-called may be combined to consider a more stringent definition of a no-show. They will also be analyzed separately. We expect the intervention to have an effect on the no-shows, not attended-called, late-screened, late-turned away and ineligible categories and will evaluate that effect separately. Sub-categories will be compared using chi-square tests to determine differences in outcomes between groups (control and intervention). Data from the CFIR survey will be analyzed using descriptive statistics and in the regression models to evaluate which constructs are related to implementation outcomes. Data analysis will be conducted in Stata (Stata Corp., College Station, TX).

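### The chi-square tests of appointment sub-categories adjust for neither clinic nor calendar time; read as pooled tests, their error exceeds 5% by an amount that depends on enrolment, ICC and trend

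*Protocol article*

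**What the plan says.** Under Outcome measures, the protocol article makes appointment adherence the primary outcome and divides it into categories such as no-show, late-screened and ineligible. Two methods are then given for these data under Statistical methods.

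- The model: "Due to the correlated nature of the data and repeated observations taken on each clinic", the plan chooses GEE: "generalized estimating equations (GEE) will be used to model outcomes while allowing us to control for potential confounders". Time is among the example confounders.
- The simple test: "Sub-categories will be compared using chi-square tests to determine differences in outcomes between groups (control and intervention"). No clinic or time term is mentioned.

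Two other places bear on the role of the simple test. The abstract says "Data will be analyzed using descriptive statistics (chi-square tests) and generalized estimating equations (GEE"), which classes the chi-square tests as description. The Blinding section says that "the analysis is designed as a time series in which every clinic receives the intervention rather than a comparison between groups". Outcome measures also promises control of confounders because start dates cannot be randomized. Randomization and allocation says that clinics start in groups of three, on dates set by operational constraints.

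**The concern.** A standard chi-square test assumes independent women. Here the women come from nine clinics, and the protocol itself plans on an average ICC of 0.06. In a stepped wedge, clinics that start early contribute a larger share of their own observation time to the intervention condition, and late starters a larger share to control. A pooled comparison therefore mixes clinics in different proportions and treats between-clinic differences as if they were sampling noise between women. Intervention time is also later on average, so any drift in attendance is carried into the comparison.

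At stake are the p-values for the individual categories. The same paragraph expects effects on five of them and intends to evaluate each separately. No-show is one of the five and is also the endpoint used for the sample size. The Blinding section reserves the exploratory label for analyses that were not pre-specified, so a pre-specified chi-square test could be reported as hypothesis testing.

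**Working it through.** **Inputs from the protocol article.** Nine clinics in three groups of three; 466 women planned (Sample size); about 2,200 anticipated (Trial status); ICC average 0.06, reported range 0.0009 to 0.22; no-show 35% falling to 28%.

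**Assumed inputs.** Fig. 1 is not shown, so I take four equal periods with 1, 2 and 3 control periods for the three groups, equal numbers of women per clinic-period, and a 35% outcome. The documents give no secular trend; I use none, then 1 and 2 points per step.

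**Step 1: the plan's own figure.** The plan says "an α of 0.05 and a power of 0.9 equals 924 per group", "assuming a baseline no-show rate of 35 % reduced to 28" per cent. The two-sided formula with pooled variance gives

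n = [1.960 × √(2 × 0.315 × 0.685) + 1.2816 × √(0.35 × 0.65 + 0.28 × 0.72)]² / 0.07² = 923.3, rounded up to 924.

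This reproduces. It is a calculation for independent women; the plan states no error rate for the chi-square tests.

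**Step 2: variance inflation of the pooled test.** There are 3 × (1 + 2 + 3) = 18 control and 18 intervention clinic-periods. A clinic's effect enters the intervention-minus-control difference with weight 3/18 − 1/18 = 1/9 (early group), 0 (middle) or −1/9 (late). The squared weights sum to 6/81. Relative to the variance that the chi-square test assumes,

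VI = (1 − ICC) + ICC × (6/81) × N/4,

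and the true rejection rate at a nominal 5% is 2 × [1 − Φ(1.96/√VI)].

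| ICC | N = 466: VI, error | N = 2,200: VI, error |
|---|---|---|
| 0.0009 | 1.01, 5.1% | 1.04, 5.4% |
| 0.006 | 1.05, 5.5% | 1.24, 7.8% |
| 0.06 | 1.46, 10.5% | 3.38, 28.7% |
| 0.1 | 1.76, 14.0% | 4.97, 37.9% |
| 0.22 | 2.68, 23.1% | 9.74, 53.0% |

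Simulation with no true effect agrees: about 11% and 30% at ICC 0.06 on the proportion scale. With the ICC defined on the logit scale the rates are lower, about 9-10% and 24%. Hence about 9-11% and 24-29%. Other layouts at ICC 0.06 (more periods, unequal splits) give 7-19% for 466 women and 18-46% for 2,200.

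**Step 3: calendar time.** Under the assumed layout the mean period is (2×3 + 3×6 + 4×9)/18 = 3.33 for intervention and (1×9 + 2×6 + 3×3)/18 = 1.67 for control, a gap of 1.67 periods. A fall of 2 points per step therefore adds a spurious difference of 3.33 points. At 2,200 women the chi-square standard error is √(4 × 0.35 × 0.65/2,200) = 2.03 points, so the statistic shifts by 1.64. With VI 3.38 the rejection rate is 45.6% (about 43-44% on the logit scale). A fall of 1 point per step gives 33% (29% on the logit scale). At 466 women, 2 points per step gives 17%.

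**Step 4: would stratifying by clinic suffice?** In simulation at 2,200 women and ICC 0.06, a clinic-stratified test rejected in 5.3% with no trend and a constant clinic effect. It rejected in 13.5% when the clinic effect varied between periods (autocorrelation 0.8), and in 36% with a constant clinic effect and a total fall of 5 points. An analysis of clinic-period proportions with clinic and period effects stayed at 4.3-5.6% in every scenario tried.

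**The case against.** The strongest reply is that these tests carry little weight. The abstract labels them descriptive, GEE is the stated outcome model, and the regression is to include confounder control: "regression modeling will be used to evaluate outcomes while allowing for control of potential confounders (e.g., time, clinic size, staffing" and others). The paragraph does not say which method will carry the separate evaluation of category effects, so chi-square has not been shown to replace GEE there. This stands, and it confines the point to the sub-category tests. It does not remove the purpose stated under Statistical methods, which is to determine differences and not to describe counts.

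A second reply is that pooling is only a reading. Outcome measures speaks of comparing the intervention period with the baseline period in each clinic, and a chi-square within clinics would remove the clinic-mix component, which is all of the no-trend inflation when clinic effects are constant. This also stands, but such a test still confounds the programme with calendar time (Step 4).

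A third reply is that the size depends on inputs the documents do not give: layout, trend, and the rates and ICCs of categories other than no-show. That is correct. A reader might infer a fixed error rate of 24-44%. The documents do not support that: the lower end needs 2,200 women at ICC 0.06, and the upper end needs an assumed trend as well. A reader might also infer that any secular change would be reported as a programme effect. The planned GEE, with time among its example confounders, contradicts this for the main analysis.

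**Conclusion.** The point holds for the sub-category chi-square tests. As written they ignore the correlation that the same paragraph gives as the reason for GEE, they leave out the confounder control promised because start dates are not randomized, and their status differs between the abstract and Statistical methods.

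Read as pooled tests, they reject too often. The error is about twice nominal at the planned sample size and average ICC, and about five to six times nominal at the anticipated enrolment, with no trend and four equal periods assumed. It is close to nominal if the ICC is very small and there is no trend. It is well above nominal even at a small ICC if there is a trend: at ICC 0.006 and 2,200 women, an assumed fall of 2 points per step gives about 39%. The figures are for a 35% outcome such as no-show and should not be carried over to the rarer categories without their own rates. The main GEE analysis of adherence is not called into question here.

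**What to change.** Replace the chi-square sentence under Statistical methods. Test each sub-category in the planned GEE as a binary outcome, with adjustment for clinic and period, and with standard errors and reference distribution suited to nine clusters. Show raw counts and percentages by condition as description only, without chi-square p-values, so that the section agrees with the abstract. Stratifying the chi-square by clinic would be only a partial remedy, because calendar time stays unadjusted.

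The cost is one changed sentence, a few more runs of a model already planned, and less precise (wider) intervals for the sub-categories. The article reports that clinics were still collecting baseline measures, so from that position the change could precede the outcome analysis.

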### Outcome measures

The primary outcome measure will be appointment adherence comparing the intervention period to the baseline period in each clinic. Appointment adherence will be considered using the following categories: no-show, not attended-called, late-screened, late-turned away, canceled/re-scheduled, and ineligible. A no-show will be considered a patient who makes no contact with the clinic prior to the appointment and does not attend on the day of mammography screening. A not attended-called is a patient who calls the clinic the day of the screening and asks to cancel or re-schedule (this may occur before or after their designated appointment time). Late-screened is a patient who arrives more than 30-min late for their appointment but is still seen by the mammography provided (e.g., worked in). Late-turned away is a patient who is more than 30-min late for their appointment and is turned away by the provider. A cancel or re-schedule is a patient who calls more than 24 h in advance to cancel or change their appointment date. An ineligible patient is a woman with symptoms who is ineligible to receive a screening mammogram and is turned away for a diagnostic evaluation or a woman who is turned away for incomplete paperwork. These categories are based on an assessment of the mammography providers’ and clinics’ behavior and the ways in which patient appointment outcomes are considered within a clinic system. Secondary measures will include patient referral to diagnostic (following screening) as a binary outcome and amount of time the referral took in days, patient referral to treatment as a binary outcome and the amount of time it took in days, and measures of implementation in each clinic based on the consolidated framework for implementation research (CFIR). A survey made up of scales assessing various CFIR constructs was developed by the Cancer Prevention and Control Research Network (CPCRN); we will use several scales from that survey in this study. These constructs will be measured at baseline (adoption), 8-week post-implementation, and following the end of the trial period (sustainment) [35–37]. Because randomization of start dates is not possible, we will control for potential confounders in the analysis of the data. Control variables may include time to intervention start date in each clinic, clinic size, staffing, and whether or not the clinic had a pre-existing patient navigation program for breast cancer screening, patient demographics, region served, and infrastructure characteristics (e.g., funding) (taken from the Health Resources and Services Administration Uniform Data System (UDS) reports for FQHCs and our economic survey).

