
### Trial status

The trial has completed enrollment of the first wave of clinics (*n* = 9) and is currently collecting baseline measures at these locations. Baseline measures include appointment adherence outcomes as described above, the clinic and patient resource utilization survey for the budget impact analysis, and CFIR survey. All participating clinics have completed the baseline CFIR survey. Based on the number of mammography screening drives at each clinic, we anticipate enrolling approximately 2200 women into the first wave of the trial.

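### Nine clinics cannot reliably show which of several CFIR constructs are related to implementation, so the planned construct regressions should be descriptive and labelled exploratory

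*Protocol article*

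**What the plan says.** All references are to the protocol article.

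- **Purpose of the regressions (Statistical methods).** CFIR data will be described and also used "in the regression models to evaluate which constructs are related to implementation outcomes".
- **Method (Statistical methods).** The only regression approach given is GEE: "generalized estimating equations (GEE) will be used to model outcomes while allowing us to control for potential confounders". The adjustment variables listed as examples are "time, clinic size, staffing, and whether or not the clinic had a pre-existing patient navigation program". Apart from time, these are clinic characteristics.
- **Constructs (Outcome measures).** The CFIR measures are secondary measures of implementation in each clinic. On how many there are, the text says only "we will use several scales from that survey in this study". They are taken three times: at baseline, 8 weeks after implementation, and after the trial period.
- **Clinics.** Sample size plans for "466 women across nine clinics". Trial status reports: "The trial has completed enrollment of the first wave of clinics", also nine. No later wave is described or sized.
- **Exploratory label (Blinding).** It is reserved for analyses that were not pre-specified. The CFIR regression is announced and carries no such label.

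**The concern.** A CFIR score belongs to a clinic, so the information on whether a construct goes with better implementation comes mainly from differences between nine clinics. Recruiting more women, or surveying more staff per clinic, does not add clinics. GEE relies on a robust variance that is justified when clusters are many. With nine clusters and several clinic-level covariates it is too small, and the tests reject too often. Other clinics could then be told that certain constructs drive implementation when the data cannot show it. As nothing marks the analysis exploratory, readers could take the results as tested findings.

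**Working it through.** **The plan's own figures.** For 35% versus 28%, two-sided alpha 0.05 and power 0.90, the two-proportion formula (pooled variance, no continuity correction) gives 924 per group, as stated, or 1848 in total. Then 1848 × 0.21 = 388, and 388 × 1.2 = 466 women. The design effect itself cannot be checked, because its step and cluster-size inputs are not in the text. These figures concern the no-show comparison. The article gives no power or error rate for the CFIR regressions.

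**Inputs.** Nine clinics and ICC 0.06 (Sample size). Women per clinic: 466/9 ≈ 52 from Sample size, or 2200/9 ≈ 244 from Trial status. Assumed, because not stated: one, three or five constructs; a 5% threshold; uncorrected sandwich errors. The simulated outcome is no-show, as implementation outcomes are not defined.

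**Degrees of freedom.** An intercept plus clinic size, staffing and prior navigation uses 4 of 9 clinic-level degrees of freedom, leaving 9 − 4 = 5. Five constructs fixed per clinic would use all of them.

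**False positives with no true relation.** Logistic GEE, independence working correlation, reject if |estimate/robust SE| > 1.96. Constructs are independent, fixed per clinic and entered jointly, with no confounders. Repeated runs of 2,000 to 3,000 simulations gave:

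| Constructs | Error per construct | At least one false relation |
|---|---|---|
| 1 | 18–21% | 18–21% |
| 3 | 26–28% | 50–57% |
| 5 | 40–43% | 78–81% |

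The rates barely change with the ICC (0.006 to 0.22) or with 52 or 244 women per clinic; the number of clinics drives them. Testing one construct at a time, still uncorrected, gives at least one false relation in 45–50% of trials with three constructs and 63–67% with five.

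**Adding the three named clinic-level confounders.** Error per construct is 31–34% with one construct and 49–52% with three, depending on whether a simple K/(K−1) variance factor is applied.

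**Letting constructs change within clinic.** With three time points and 30–50% of construct variance within clinic (an assumption), error per construct falls from 28% to 20–23% with three and from 41% to 23–27% with five. At least one false relation with five still occurs in 69–74% of trials.

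**With a small-sample correction.** A bias-reduced variance cut single-construct error from 18.5% to 6.5% (200 runs). A leave-one-cluster-out variance with t critical values gave about 2–6%. Power is then the limit. With one value per clinic and a t-test on 7 df, power is 0.12, 0.29 and 0.62 for true correlations of 0.3, 0.5 and 0.7. Even at a true 5% level, the chance of at least one false relation is 1 − 0.95³ = 14% with three constructs and 1 − 0.95⁵ = 23% with five.

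**Correlation needed for p < 0.05 at n = 9.** Pearson: 2.365/√(2.365² + 7) = 0.67. Spearman, by exact enumeration: 0.667 gives p = 0.059, 0.683 gives p = 0.0503 and 0.70 gives p = 0.043, so about 0.70.

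**Share of declared relations that are false.** If one of m constructs is truly related, the share is (m − 1)a/[(m − 1)a + power], where a is the error per null construct. For three joint constructs and a true correlation of 0.5: 2 × 0.275/(2 × 0.275 + 0.545) = 50%. For five: 4 × 0.406/(4 × 0.406 + 0.590) = 73%. Over single or joint entry and true correlations of 0.5 or 0.7, the range is 32–50% with three constructs and 52–73% with five.

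**The case against.** The article does not say that the scales enter together, that uncorrected errors are used, or that p < 0.05 selects constructs. Such details are commonly left to an analysis plan that is not shown, and a correction largely removes the false positives. This stands: the high error rates are conditional, and the missing details are not the finding. What remains is the stated purpose, to find out which constructs are related. No analysis-plan wording can add clinics, and a corrected test has little power.

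The constructs are measured three times, so it would be wrong to treat them as varying only between clinics. This also stands. It lowers the rates without bringing them near 5%.

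The nine clinics are called a first wave, so more might follow. None is described, and the sample size is built on nine.

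Two stronger readings are tempting and not supported:

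- A reader might infer that most constructs declared related would be chance findings. The share calculation shows half or fewer with three constructs and one true relation. It passes half only with about five constructs, few of them truly related, and uncorrected errors.
- A reader might infer that the implementation objective fails. Trial objectives asks only for implementation at the clinics to be assessed, and the planned descriptive CFIR analysis largely serves that. Nor does the Blinding section say that every announced secondary regression is confirmatory; it simply leaves this one without an exploratory label.

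**Conclusion.** The point holds as a limit on what the construct regressions can deliver. With nine clinics, uncorrected GEE tests of clinic-level constructs would run at about four to eight times the nominal 5% (20% with one construct, 40% with five), and more with the named confounders. Corrected tests would be close to nominal but would miss a true correlation of 0.5 about 71% of the time (1 − 0.29). Neither route reliably identifies which of several constructs matter. The sizes rest on the assumed number of constructs, a 5% threshold, independent constructs, equal clinic sizes and no-show as the outcome. This is a secondary analysis; the comparison of intervention with baseline is unaffected. The change is worth making, as it needs only wording.

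**What to change.** In Statistical methods or the analysis plan:

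1. Do not enter the CFIR constructs jointly in the GEE models.
2. Report CFIR scores descriptively by clinic and time point, as is already partly planned.
3. Define the implementation outcomes. If associations with them are shown, give them one construct at a time with a confidence interval, using a small-sample method: a clinic-level correlation, or GEE with a bias-corrected variance and a t reference.
4. Label these associations exploratory and hypothesis-generating, and do not select constructs by p-value.
5. State that with nine clinics an unadjusted p < 0.05 needs an absolute correlation of about 0.67 (Pearson) or 0.70 (Spearman), before any allowance for testing several constructs.

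The cost is wording only, with no new data. The small loss is a multivariable ranking of constructs, which nine clinics could not support.
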